The intervention will be implemented using support mechanisms and ongoing evaluation within the participating clinics to ensure a harmonious integration. Interventions at the patient level will: (a) be patient-centered and educational in nature; (b) last less than three months and involve at least three encounters with CDPM practitioners; (c) include individual interviews or patient focus groups involving close relatives. The intervention will consolidate the central role of primary health care professionals and their organizations, while maintaining the natural proximity between the patient and his or her family physician. In this regard, interventions will: (a) be carried out upon referral from the primary care team; (b) allow an exchange with the primary care team and will be recorded in primary care medical records; (c) return the responsibility of long-term follow-up to the primary care team.

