#### Evaluation of effects (objective 2)

Effects will be assessed using three different strategies. To measure short-term effects, a pragmatic randomized experimental design with delayed intervention in the control group will be used [59]. The first step of randomization is the sequence generation using a simple random allocation sequence. The second step is allocation concealment by development and allocating concealment mechanism (sequentially numbered, sealed, opaque envelopes) followed by preparation of the allocation concealment mechanism using the sequence from step one. Research team members involved in generation and allocation concealment will be different from the team members involved in the implementation of assignments. Thus, the intervention group allocation system is set up so that the team member enrolling participants does not know in advance in which group the next person will be allocated.

Patients will be referred by primary care providers (family physician or nurse) to the research team who will be responsible for assessing eligibility and obtaining informed consent, as well as baseline measures (T1). For each study participant, a research assistant at the central office will open a numbered and sealed envelope. The card inside will tell if the patient will be in group A or in group B. This information will immediately be provided to the patient and subsequently to the clinical team in order to schedule the clinical interventions.

Because participants will be invited to receive the interventions in their usual clinics, blind randomization is not possible. Both patients and health care providers will know who is involved in each group, therefore we used independent (unmatched) random samples of patients to receive the intervention immediately after baseline assessments (Group A: immediate intervention group) or at the end of a three-month waiting period (Group B: delayed intervention group). We chose this randomization process because of the potential proximity of patients in and between clinics. In practice, however, we think that communication between patients of the same clinic or between clinics is scarce and will not pose a substantial threat for contamination.

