Since it is possible that participants in different groups and phases might come in contact with each other as many will be recruited in the same practice, some precautions will be taken in order to minimize the before and after evaluation biases. To prevent selection bias, the rigorous randomization methodology and allocation concealment process described previously will be respected throughout the project. The methods were reviewed and approved by the Research Ethics Board of the CSSSC and the measurement tools were validated. We expect a response rate greater than 80% and baseline measurements will be comparable in the sense that no significant differences will exist between the groups with respect to age, gender and pre-test measurements. If necessary, the statistical models will be adjusted to ensure comparability of the groups. Each subject intervention will last less than three months and the clinical intervention period is limited to 12 months in order to ensure a contemporaneous data collection.

As stated in the logic model, with the three-month delay design we seek to examine: (1) whether the immediate intervention group (Group A) will have changes at 3 months that are sustained; (2) whether there will be changes in the first 3 months before the intervention with Group B; (3) whether the short-term results of Group A will be different from those of Group B; and (4) whether the outcomes of Group A can be sustained one year later. Theoretically, it is anticipated that these short-term results in attitudes and behaviors of patients will be the precursors of the mid-term changes expected in the maintenance of a healthy lifestyle, quality of life and psychological well-being.

In each clinic where the intervention will be deployed, patients eligible to receive the intervention must be between 18 and 75 years of age and present at least one of the following conditions: diabetes, cardiovascular disease, chronic obstructive pulmonary disease (COPD), asthma or risk factors (smoking, obesity, dyslipidemia, glucose intolerance, and metabolic syndrome). Patients with serious cognitive problems will be excluded.

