To comply with the pragmatic nature of the intervention, it is up to the referring professional (primary care physician or nurse) to determine eligibility. For each patient, the referring professional will request the patient’s authorization to disclose his or her contact information to the research team and then complete a referral form. Patients refusing to take part in the study will still be eligible to receive the intervention without being involved in the evaluation process. Two patients from the same family can receive the intervention, but only one (randomly selected) will be asked to participate in the research project.

Patients agreeing to participate will complete an initial set of questionnaires at baseline (T1) collecting the main variables and sociodemographic data. Patients will be randomized to receive either the intervention within a short period of time (Group A) or later (three months later for Group B). At time 2 (T2), which will occur three months after the intervention for Group A or immediately before the intervention for Group B, patients will complete the second evaluation questionnaire. Baseline measures will be used to document equivalence between groups while T2 measures will enable the assessment of the effect after three months. A short questionnaire documenting co-interventions will also be administered at T2 (Table 3). Co-interventions represent any additional health care or CDPM services and/or therapeutic procedures other than those that are formally included in the study and may introduce confounding variables that could potentially affect the validity of the results of this study.

**Table 3 T3:** Variables and outcome measures

**Short-term:** Key measurements of effect (measured at T1 and T2 in Groups A and B)	
Self efficacy	The Self-Efficacy for Managing Chronic Disease (SEM-CD) scale (6 items) developed by the Stanford Patient Education Research Center [67].
Empowerment	Proxy of “The Health Education Impact questionnaire (heiQ)” [77]
Comorbidity	The Disease Burden Morbidity assessment (DBMA) [64]
**Mid-term:** Key measurements of effect (measured at T1 and T3 in Groups A and C)	
Health behaviour	Behaviour Risk Factor Survey System Questionnaire (eating habits, physical activity, smoking and alcohol consumption) [65]
Functional health status/quality of life	SF -12 [63,78]
Psychological well-being	K-6 [62]
Comorbidity	The Disease Burden Morbidity Assessment (DBMA) [64]

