### Limitations and biases

Although conducting a randomized clinical trial may present a challenge in clinical settings where some patients receive an intervention (Group A) while others are waiting for the intervention (Group B), the short period of time between randomization and the second measurement will limit the possibility of co-interventions and maturation biases. Nonetheless, given the pragmatic nature of the trial, patients will be free to seek information beyond the proposed intervention. This may contribute to improve the observed effect. Co-interventions will be evaluated by questionnaire and will be taken into account in the analysis. In addition, analysis of the implementation will bring qualitative insight to this phenomenon. The repetition of the questionnaires may induce a learning effect; however, the time between each execution is long enough to reduce it.

The study design and its short term outcomes measure have been developed specifically to address the problem of the short period between T1 and T2. The project’s proposed two-year timeframe does not allow any exploration of the long-term efficacy of interventions on the use of the health care system.

The intervention may differ from one setting to another, but action will be taken to minimize this risk. We will outline the major considerations that may contribute to a variation in intervention or its fidelity at each stage.

The decision to measure psychosocial outcomes only is based on theoretical reasons that such outcomes are particularly pertinent to examine the adoption and maintenance of a healthy lifestyle and a better quality of life.

One potential bias is the recruitment bias, where health care providers recruit differently depending on their practice, which leads to selection bias and lack of comparability [76]. Recruitment for the present study is prior to allocation which will be provided by the research team. We will pay particular attention to find out whether patients are comparable from one participating setting to another as each primary health care professional will select and refer his or her patients and each participating setting has its own distinct contextual variables.

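### T2 has a different anchor in each randomised arm; read plainly, it falls later in Group A than in Group B and conflicts with the three-month T2 described elsewhere

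*Protocol article*

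**What the plan says.** All places are in the protocol article.

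- **Definition of T2** (Evaluation of effects, objective 2): "At time 2 (T2), which will occur three months after the intervention for Group A or immediately before the intervention for Group B".
- **Start of the intervention** (same section): patients are randomised to "receive the intervention immediately after baseline assessments (Group A: immediate intervention group) or at the end of a three-month waiting period". A later sentence is looser: "Patients will be randomized to receive either the intervention within a short period of time (Group A) or later (three months later for Group B".
- **Length of the intervention**: the Intervention section says it will "last less than three months and involve at least three encounters with CDPM practitioners". The evaluation section repeats the limit: "Each subject intervention will last less than three months".
- **T2 as a three-month assessment** (evaluation section): one aim of the delay design is to see "whether the immediate intervention group (Group A) will have changes at 3 months that are sustained". Shortly after the definition of T2 the text adds that "T2 measures will enable the assessment of the effect after three months".
- **Use made of the interval** (Limitations and biases): "the short period of time between randomization and the second measurement will limit the possibility of co-interventions and maturation biases". No difference between arms is mentioned.
- **Analysis** (Data analysis under objective 2): Groups A and B are compared on T2 scores by ANCOVA adjusted for T1 scores.
- **T3, for contrast**: this visit is set at one year from T1, a fixed interval from baseline.

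**The concern.** In a randomised comparison with a delayed-intervention control, both arms should be assessed at the same time since randomisation. The definition of T2 instead ties the visit to the intervention, and does so differently by arm: after it in Group A, before it in Group B. The intervention is a course of at least three encounters over a period of weeks to months, so a visit three months after it most naturally means three months after the course is over. That would put Group A's visit later than Group B's.

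The comparison at T2 is the only randomised one in the study. If follow-up is longer in one arm, whatever changes with time during the extra interval becomes part of the estimated treatment effect: natural drift, further regression to the mean after referral, season, or added contact with other services. Adjustment for T1 corrects for where patients started, not for how long they were followed. The argument in the limitations section that a short interval restrains maturation and co-interventions would also be weaker for Group A than for Group B.

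**Working it through.** **1. The plan's own figures.** These reproduce, and the point does not touch them.

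- Proportions 35% versus 20%, two-sided 5%, 80% power, pooled variance without continuity correction: 138 per group.
- Drop-out of 15%: 138 / (1 − 0.15) = 162.4, rounded up to 163 per group, or 326 in total.
- Detectable standardised difference with 138 per group: (1.960 + 0.842) × √(2/138) = 0.337, which agrees with the stated 0.34.

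**2. Months from T1 to T2.** Let s be the delay from T1 to the start of the intervention in Group A (about 0, as it starts right after baseline) and d the length of the intervention (0 < d < 3).

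- Group B, measured at the end of its wait: 3.
- Group A, three months counted from the end of the intervention: s + d + 3.
- Group A, three months counted from the start: s + 3.

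| d (months) | A, from end | A, from start | B | Gap, from end | Gap, from start |
|---|---|---|---|---|---|
| 1 | 4 | 3 | 3 | 1 | 0 |
| 2 | 5 | 3 | 3 | 2 | 0 |
| just under 3 | almost 6 | 3 | 3 | just under 3 | 0 |

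(The table takes s = 0.) On the plain reading the gap equals each patient's own intervention length, so it varies between patients and is always under three months. On the from-start reading the gap is only the start delay s.

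**3. Consistency.** A Group A visit at 4 to almost 6 months does not fit an aim about Group A's changes at 3 months, nor a T2 that shows the effect after three months, nor a single short interval from randomisation to T2. The from-start reading fits all three, but no sentence states it.

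**4. Possible size, plain reading only.** Assume no treatment effect and a common untreated drift of r SD per month. The documents give no value for r; 0.01 to 0.05 is an assumption for illustration. Bias = r × gap. With 138 per group and no gain from covariate adjustment, the standard error is √(2/138) = 0.120 SD. The rejection rate of the nominal 5% test is Φ(bias/SE − 1.96) + Φ(−bias/SE − 1.96).

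| r (SD/month) | Gap (months) | Bias (SD) | Bias / 0.34 | Rejection rate |
|---|---|---|---|---|
| 0.01 | 1 | 0.01 | 3% | 5.1% |
| 0.05 | 1 | 0.05 | 15% | 7.0% |
| 0.01 | 3 (limit) | 0.03 | 9% | 5.7% |
| 0.05 | 3 (limit) | 0.15 | 44% | 23.8% |

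The 3-month rows are an upper limit, because they give every Group A patient the longest possible intervention.

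**The case against.** The strongest reply is that one loosely worded sentence is being set against a document that otherwise points to a common three-month T2. The sentence never says that the three months run from the end of the intervention. Counted from the start, with Group A starting right after baseline, both arms are measured at about three months, and the remaining statements agree. The study timeline (Figure 2) could not be seen and may show exactly that. This stands: a reader might infer that unequal follow-up is an established feature of the design, and the documents do not support that. It is the plain reading of a definition that conflicts with other text.

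A reader might also infer that every time effect is fully confounded with treatment. That goes too far. Even on the plain reading, both arms share the first three months of drift and regression to the mean, and only the extra interval differs. Co-interventions are recorded by questionnaire at T2 and are to be taken into account in the analysis. This helps with one of the channels, though it does not adjust for elapsed time as such.

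Nor do the documents support a claim that the bias must be large. They contain no drift rate, and the gap may be well below three months.

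What the reply does not remove is the conflict itself. Staff who schedule visits from the definition could reasonably do so either way. Even on the from-start reading, T2 is tied to when the intervention begins and not to T1, so delays in starting would move it.

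**Conclusion.** The point holds as an internal contradiction that bears on the main randomised comparison. T2 is defined by different anchors in the two arms. Read plainly, that gives just over 3 to almost 6 months from T1 in Group A against about 3 months in Group B, contrary to the three-month T2 stated elsewhere in the article. If this reading is followed, the ANCOVA at T2 mixes the treatment effect with up to just under three months of extra elapsed time in Group A.

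The size is illustrative. Under the assumed drift of 0.01 to 0.05 SD per month, the bias runs from 0.01 to 0.05 SD at a 1-month gap and reaches 0.03 to 0.15 SD at the 3-month limit, against a detectable effect of 0.34. If the three months run from the start of the intervention, the gap is close to nil and only the wording needs repair. Which reading was intended cannot be decided from the available text.

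**What to change.** Reconcile the definition of T2 with the aims of the delay design, the statement on the effect after three months, and the limitations section. Define T2 in both arms as the same interval from T1 or randomisation, three months as those statements imply, with one common visit window. In Group B it is taken before the first encounter. This gives T2 the kind of anchor that T3 already has. Check that Figure 2 agrees. If a measurement three months after completion is wanted in Group A, keep it as a separate descriptive assessment outside the A–B ANCOVA.

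The cost is a sentence and a visit window; the sample size stays at 326. There is a real downside: because the intervention may take almost three months and may not start on the day of baseline, some Group A patients will be measured just after, or shortly before, they complete it. The A–B contrast then estimates the effect at three months from randomisation, not the effect three months after a completed course, and the report should say so.

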**Other variables**	
Participant characteristics	Sex, age, socioeconomic status, education, referral diagnosis
Co-intervention	Questionnaire on co-interventions

To document the effect over a year (mid-term), a repeated measures design is proposed. Thus, all patients in Group A will be reassessed a third time (T3), one year after T1. The T3 questionnaire will be identical to the one used at T1 and T2 (Figure 2).

**Figure 2 F2:**
[figure not shown]
Study timeline.

Finally, a quasi-experimental design with a non-equivalent group will be used to evaluate mid-term effects. The control group (Group C) will come from the PRECISE research program platform (main investigators: [name] and [name], http://www.programmeprecise.ca) [61]. The PRECISE study is a cohort of 2197 adults aged 25-to-75 years followed for 4 years. The target population is community-dwelling adults undifferentiated by disease, who sought primary health care locally, did not suffer from major cognitive impairment, and were able to respond to written and oral questions in English or French. Participants were randomly selected within the geographic boundaries of four local health care networks in Québec (Canada). At recruitment (T0), cohort participants reported on sociodemographic information, functional health and health care use. Two weeks (T1), 3 months (T2) and 12 months (T3) after recruitment, they completed a self-report questionnaire on their current health, health behaviours and primary health care experience in the previous year. Use of medical services is confirmed through the review of administrative databases. As in the present study, the PRECISE cohort’s main dependent variable is functional health status and quality of life which are measured with the second version of the Short-Form-12 survey (SF-12v2) [62,63]. Comorbidity is measured using the validated Disease Burden Morbidity Assessment [64]. Lifestyle and health behaviour (eating habits, physical activity, smoking and alcohol consumption) are measured using the Behavioral Risk Factor Survey System Questionnaire [65]. This unique longitudinal cohort in Canada that is providing valuable information on the effectiveness of care in the general population rather than in clients of selected care models will offer us the opportunity to measure health care experience and to quantify the impact of introducing different models of CDPM services.

Patients from this cohort will be matched with patients from Group A by age, gender, diagnosis and family income. Groups will be compared on the basis of changes over a year.

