### Feasibility

After a six-month implementation phase, the study will take place over 18 months and will involve eight medical clinics. To recruit 326 patients for the study and meet the minimal time between intervention and effects in one year, patient selection will need to be done within six months. At the very conservative mean rate of two patients per week per clinic, this objective should be easily achieved. Pairing 138 patients with the PRECISE cohort with a potential pool of 2197 patients from the waiting rooms of medical practices is feasible. With regard to health care providers in clinical settings, a survey was conducted in September 2010 that showed their willingness to participate.

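### The matched cohort for the one-year comparison starts at age 25 while the trial admits from 18, and neither the diagnosis used for matching nor the number of usable controls is tied to the trial's criteria

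*Protocol article*

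**What the plan says.** Under *Evaluation of effects (objective 2)*, the Protocol article sets the trial's entry criteria: "patients eligible to receive the intervention must be between 18 and 75 years of age and present at least one of the following conditions". The list covers diabetes, cardiovascular disease, COPD, asthma and a set of risk factors. All of Group A is to be measured again one year after T1.

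The same section describes the source of Group C: "The PRECISE study is a cohort of 2197 adults aged 25-to-75 years followed for 4 years". It adds: "The target population is community-dwelling adults undifferentiated by disease, who sought primary health care locally". Members were sampled at random within the areas of four local health care networks. The link to Group A is: "Patients from this cohort will be matched with patients from Group A by age, gender, diagnosis and family income".

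The quantitative *Data analysis* section compares A and C at T3 by ANCOVA. The model adjusts for T1 scores and for non-equivalent baseline characteristics, and a parenthesis limits the latter to variables not used for matching. The groups are treated as independent.

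Table 3 lists referral diagnosis among participant characteristics, and lists the DBMA as measured at T1 and T3 in Groups A and C.

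*Sample size and statistical power* plans 138 Group A subjects against the same number from the cohort, with a detectable effect size of 0.34. *Feasibility* concludes: "Pairing 138 patients with the PRECISE cohort with a potential pool of 2197 patients from the waiting rooms of medical practices is feasible".

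**The concern.** Three features of the A–C comparison do not fit together.

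- **Age.** The trial's lower limit is 18 and the cohort's is 25. The article does not restrict the A–C set to the shared range. A patient aged 18 to 24 must either leave the comparison or be paired with someone older. In the second case the planned model offers no correction, because age is a matching variable and is therefore outside the stated adjustment set.
- **Diagnosis.** This is the variable meant to pick comparable controls out of a general cohort, yet the article does not say what it is built from. The only diagnosis variable named for trial patients is the referral diagnosis. Randomly sampled cohort members were not referred and would not have one.
- **Pool.** The feasibility statement counts the full cohort, not the members who have a qualifying condition.

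A versus C is the only controlled comparison for health behaviour, SF-12 and K-6 at one year. Non-overlap in age, or disease status ascertained differently in the two groups, would affect the estimate directly, and there is no randomisation to fall back on.

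**Working it through.** **1. The plan's own figures reproduce.** Inputs from *Sample size and statistical power*: 35% versus 20% improving, two-sided α = 0.05, power 80%, drop-out 15%.

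- Two proportions, pooled variance, no continuity correction: n = [1.96·√(2·0.275·0.725) + 0.8416·√(0.35·0.65 + 0.20·0.80)]² / 0.15² = (1.2377 + 0.5239)² / 0.0225 = 137.9, so 138 per group.
- Drop-out: 138 / 0.85 = 162.4, so 163 per group and 326 in total.
- Detectable effect size with 138 per group: (1.96 + 0.8416)·√(2/138) = 0.337 by the normal approximation and 0.338 by the two-sample t-test. The plan states 0.34. Power at 0.34 is 80.4% (t-test).

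**2. Age overlap.**

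| | Trial (Group A) | Cohort (Group C) |
|---|---|---|
| Age range | 18–75 | 25–75 |
| Disease criterion | at least one listed disease or risk factor | none |

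The band 18–24 exists only in Group A. An 18-year-old is at least 25 − 18 = 7 years from the nearest possible control.

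**3. Does the analysis repair it?** The ANCOVA covariates are T1 scores plus baseline characteristics not used for matching. Age, gender, diagnosis and income are matching variables, so as written they are left out. An inexact match on age or diagnosis stays in the estimate, except for what T1 scores absorb.

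**4. Size of the loss if unmatched patients leave.** The share under 25 is not in the document, so 3% to 10% is an assumption.

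| Assumed share under 25 | Patients lost from 138 | Remaining per group | Detectable effect size (t-test) | Power at 0.34 |
|---|---|---|---|---|
| 0% | 0 | 138 | 0.338 | 80.4% |
| 3% | 4 | 134 | 0.344 | 79.2% |
| 10% | 14 | 124 | 0.357 | 76.0% |

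**5. Size of the usable pool.** The share of the cohort with a qualifying condition is also not given. Assumed shares, before matching on age, gender and income:

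| Assumed share qualifying | Candidates out of 2197 | Candidates per Group A patient (138) |
|---|---|---|
| 10% | about 220 | 1.6 |
| 30% | about 659 | 4.8 |
| 50% | about 1098 | 8.0 |
| 70% | about 1538 | 11.1 |

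The pool falls below 138 only if fewer than 138 / 2197 = 6.3% qualify, and below 163 only if fewer than 163 / 2197 = 7.4% do.

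**6. Source of diagnosis.** Referral diagnosis can exist in Group A only. The DBMA is collected in both groups, and *Variables and outcome measures* says it will be used to characterise patients in the different groups. A common source is therefore available but is not named as the matching variable.

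**The case against.** The best defence is that the plan is open about this. It calls Group C non-equivalent, speaks only of a potential pool, and matches on diagnosis, which is the ordinary way to select diseased controls from a general cohort. A journal article can leave the age caliper and the handling of unmatched patients to the full protocol or analysis plan. Few patients in this population may be under 25, and the power loss is small under any plausible share. The comparison is not the randomised one, and a within-group repeated-measures analysis of Group A also addresses the one-year question.

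Much of this stands, and it rules out several stronger readings that a reader might infer:

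- *That some Group A patients certainly cannot be matched.* This requires patients aged 18–24 to enrol and age to be matched closely. The article allows the first without quantifying it and is silent on the second.
- *That an undifferentiated cohort makes the groups differ in morbidity by construction.* Matching on diagnosis is there to prevent this. The lack of a disease criterion shrinks the pool; it does not by itself make patients unmatchable.
- *That every pair sets a clinician's referral label against self-report.* The article never says that referral diagnosis is the matching label. It fails to say what is.
- *That pairing is infeasible.* At assumed shares of 10% to 70%, candidates still outnumber 138 before the other matching variables are applied.

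What the defence does not answer is that the article itself fixes an age range for Group C that does not cover Group A, together with an adjustment set that leaves out the matching variables. A caliper set elsewhere cannot create controls under 25. The within-Group A analysis has no control group.

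The waiting-room phrase in *Feasibility* and the random geographic sampling described earlier may both be true, since members had sought primary care locally. That is an editorial point.

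**Conclusion.** The point holds in a limited form. Any Group A patient under 25 has no same-age control, and the planned ANCOVA would not adjust for the resulting age difference. The number affected is not given and is probably small. The diagnosis variable lacks a stated common source, although one is at hand. The figure of 2197 does not show how many cohort members have a qualifying condition, so it neither supports nor refutes feasibility.

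The main consequence is for comparability in the only controlled one-year comparison. The effect on precision is modest: the detectable effect size rises by roughly 0.005 to 0.019 (0.344 − 0.338 in rounded figures, and 0.357 − 0.338). This rests on the assumed 3% to 10% under 25 and on 138 evaluable patients. The short-term randomised comparison of A with B is untouched.

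**What to change.** 1. Define the A–C set as Group A patients aged 25–75 at T1 and their matches. Keep patients aged 18–24 in the A–B and within-A analyses.
2. Build the diagnosis matching variable from the DBMA in both groups, supplemented by items that both studies collect, such as smoking. First check which of the trial's risk factors those items cover; the article does not list the DBMA items, so coverage of obesity, dyslipidemia, glucose intolerance and metabolic syndrome is unknown.
3. Apply the trial's condition and risk-factor criterion to the cohort before matching, as far as its data allow.
4. Add age and diagnosis to the A–C ANCOVA if matching on them is inexact.
5. In *Feasibility*, report the resulting eligible count beside or in place of 2197, and give one account of how the cohort was sampled.

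The cost is some protocol wording and a check and query of an existing database. A few Group A patients leave the A–C comparison, with the small loss of precision shown above, and the quoted pool becomes smaller. If the cohort data do not record some risk factors, the screen in step 3 will be incomplete and the report should say so.
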